#### Sample Size Estimates

Common algorithms do not exist for assessing power for complex SEM; however, 3 aspects of sample size were considered. First, because of the iterative and complex nature of SEMs, it was important to verify that the sample size was sufficiently large to produce stable model estimates. There are simulation studies suggesting that for models of the size and complexity proposed, minimum sample sizes for model stability would likely be in the hundreds [64]. Second, comparing models requires a certain sample size. Published estimates of model degrees of freedom suggest that sample sizes in the hundreds would be sufficient to discriminate competing models [64]. Finally, given a set sample size, an expected detectable effect size was estimated. Setting statistical significance at =.05 (2-sided tests) and power at 80%, a sample size of 500, for example, would allow detection effects of approximately 0.13 SD units across time (ie, considered a small effect). Even accounting for losses due to missing data, which can become an issue when combining multiple sources of data at multiple levels, the proposed sample size of 1200 patients, and the smaller number of clinician and practice environments in which they were nested, should be sufficient to estimate stable, comprehensive models and detect relatively small associations between constructs.

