**Figure 2 figure2:**
[figure not shown]
Flow diagram for establishing Consortium to Study Opioid Risks and Trends (CONSORT) criteria for opioid use.

A randomly selected group of patients meeting criteria for short-term use at day 90 were invited to participate in the study assessment. This group of patients was selected to be time-matched 1:1 to patients continuing to use opioids at day 90 (initial issue date ±2 weeks) Although it was not possible to accurately apply CONSORT criteria for short-term use until month 6 following issuance of the last prescription, the study assessment was performed at this time point to ensure that patients were captured in the earliest stages of short-term use. Because it was anticipated that the majority of the cohort would meet criteria for short-term use, it was not feasible to invite all patients to participate in the study assessment.

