#### SEM Analysis

The primary goal of aim 3 was to combine the results from aims 1 and 2 and extend these by building a statistical model that synergistically integrated the three domains of the UPOU conceptual framework. The UPOU framework has a number of complexities that limit the use of regression including multiple correlated predictors and outcomes, unobserved constructs that are difficult to directly measure, and nesting of patients with clinicians who are nested within sites. SEM can estimate latent variables and include them as both exogenous and endogenous variables in the same model, use multiple observable and quantifiable indicators to estimate latent variables from the shared variability of these indicators, and accommodate multiple endogenous variables (ie, dependent variables or outcomes) in 1 model. Multilevel SEM can estimate latent variables at 1 or more levels (eg, patient and clinician levels) and appropriately test associations at and across these different levels for categorical and continuous outcomes.

The SEMs were developed in several steps. The number of measurement models were estimated for all constructs that potentially used latent variables. Descriptive statistics were examined including means, medians, SDs, ranges, measures of central tendencies, and normality of the distributions. Extensive preliminary analyses were conducted to evaluate possible inconsistencies in the data, outliers, and variations in the data, and clinically and statistically relevant cutoff points that may facilitate the analyses were identified. The primary outcome measure was UPOU, measured as a dichotomous variable of cases and time-matched controls. The predictors of interest were grouped into 3 domains: patient characteristics, practice environment, and clinician characteristics. Each of these domains contained a number of directly observable and directly unobservable constructs. Examples of directly observable variables in the patient characteristic domain included age, sex, and employment status. Examples of directly unobservable constructs in the patient characteristic domain included symptoms of opioid withdrawal, opioid craving, and the psychosocial impact of chronic pain. Analyses (eg, coefficient α, principal components analysis, and factor analysis) were conducted to determine how to optimally combine scale items into reliable measures.

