After all measurement models were established, a comprehensive structural model describing the conceptual framework was developed. In the first step, models were fitted separately by domain. For example, a parsimonious model relating patient characteristics to UPOU was developed. This first step involved a model-testing approach to trim a saturated model containing all patient-level constructs to develop a final parsimonious model that maximally explained UPOU with the least number of parameters. The results from aim 1 analysis directly informed this stage, but models varied due to the use of latent variables and a different statistical model. The Akaike information criterion, Bayesian information criterion, and the root mean square error of approximation were used to guide decision model trimming and refinement. This process was conducted separately for all 3 domains. The second step combined the parsimonious, domain-specific models into an integrated model. This involved multilevel SEM with a patient-level outcome (eg, UPOU) and predictors at the patient level, the clinician level, and the practice environment level. This model started with the 3 parsimonious, domain-specific models but then was expanded to test for possible cross-level interactions. For example, the effects of pain management training on UPOU varied by patient age. The conceptual model, previous research, and empirical findings were used to guide the model-building process, particularly with regard to the direction of association and what interactions were tested. This was not a process for testing all possible interactions; rather, only specific indicated effect modifications were tested.

Missing data were evaluated to determine if the pattern was missing completely at random (MCAR) or missing at random (MAR). If missing data were MAR or MCAR, SEM techniques were used to estimate missing values using either full information maximum likelihood or multiple imputation. If missing data did not fit an MAR or MCAR pattern, other options were explored including pattern mixture models. To the extent possible, potential bias due to attrition and missing data over time were assessed. All analyses were conducted using Stata (version 15, StataCorp) or MPlus (version 7, Muthén & Muthén).

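### The Aim 3 detectable effect of 0.13 SD *across time* at n=500 does not describe the case-control outcome that the structural equation model analyses

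*Protocol article*

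**What the plan says.** Under Specific Aim 3, Sample Size Estimates, the article notes that no common power algorithm exists for complex SEM and gives three considerations. Two are general: samples in the hundreds should suffice for stable estimates and for comparing models. The third is the section's only effect size: "a sample size of 500, for example, would allow detection effects of approximately 0.13 SD units across time", described as small. The section then concludes that "the proposed sample size of 1200 patients, and the smaller number of clinician and practice environments in which they were nested" should be enough for stable models and for detecting fairly small relationships among constructs.

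The SEM Analysis section defines what is modelled: "The primary outcome measure was UPOU, measured as a dichotomous variable of cases and time-matched controls". The integrated model is a "multilevel SEM with a patient-level outcome (eg, UPOU) and predictors at the patient level, the clinician level, and the practice environment level". Controls come from short-term users at day 90: "This group of patients was selected to be time-matched 1:1 to patients continuing to use opioids at day 90" (Specific Aim 1, timeline section). Study Assessments sets two assessments, at 3 and 9 months, but the SEM section specifies no change between them as an outcome.

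**The concern.** The sensitivity statement is expressed as an effect over time, whereas the stated analysis contrasts cases with controls. These are different quantities with different standard errors, so the figure cannot be read as what the model can detect for UPOU.

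The figure is also the only number in that section behind the claim that fairly small associations are detectable. A reader who takes it as a case-control difference could treat a null path to UPOU as excluding effects of about 0.13 SD. The section moves without a separate figure from patients to the clinicians and practices in which they are nested, and those supply two of the framework's three domains.

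**Working it through.** **Inputs.** Two-sided α 0.05, power 0.80, n = 500, planned n = 1200 (Aim 3, Sample Size Estimates). Matching 1:1 (Aim 1, timeline section). Planned split 600/600, and correlation 0 or 0.3 (Aim 1, Sample Size Estimates). Recruited 513 cases and 517 controls (Table 1). The multiplier is k = 1.960 + 0.842 = 2.802. The 500 are taken as patients in total, which the article does not state.

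**Reproducing the article's figure.**
- One-group change, in SDs of the change: k/√500 = 2.802/22.36 = 0.125.
- Correlation or standardised coefficient, by Fisher's z: tanh(k/√497) = 0.125.
- Two independent groups of 250: k·√(2/250) = 0.251.
- Two independent groups of 500: k·√(2/500) = 0.177.

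The first two match a rounded 0.13; the last two do not.

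**Link between the two matching readings.** With a 50:50 binary outcome, r = 0.125 corresponds to d = 2r/√(1 − r²) = 0.250/0.992 = 0.25. On the correlation reading the effect is therefore the same as the 0.25 SD case-control difference, expressed on another scale.

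**Detectable case-control difference, k·√(1/n₁ + 1/n₀), and power for 0.13 SD, Φ(0.13/√(1/n₁ + 1/n₀) − 1.96).**

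| Cases/controls | Detectable difference | Power for 0.13 SD |
|---|---|---|
| 250/250 | 0.25 SD | 31% |
| 600/600 (planned) | 0.16 SD | 61% |
| 513/517 (recruited) | 0.175 SD | 55% |

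**Matched-pair variant, k·√(2(1 − r)/pairs), with r = 0.3.** For 250 pairs: 2.802·√(1.4/250) = 0.21 SD, which is 0.21/0.125 ≈ 1.7 times the one-group figure. For 600 pairs: 2.802·√(1.4/600) = 0.135 SD. The value 0.3 is borrowed from Aim 1, where it raises the detectable odds ratio. On a paired mean difference it works the other way.

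**Clinician level.** 148 clinicians completed the survey (Clinician Recruitment) against 410 to 760 anticipated (Aim 2, Sample Size Estimates): 148/410 = 36% and 148/760 = 19%. The patient-level figures do not apply to this number of units.

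**The case against.** A reader might infer that the article overstates its sensitivity for UPOU by a factor of two. The documents do not support that, for these reasons:

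- The article gives no formula or test. The one-group reading is an inference, favoured by the words *across time* but not settled by them. A standardised coefficient is a natural SEM metric and gives the same number; on that reading the factor of two is only a change of scale.
- The 0.13 is offered as an example at n = 500 and is never labelled as the sensitivity for UPOU. The SEM section allows several endogenous variables and names UPOU only as an example of a patient-level outcome, so a longitudinal use is not ruled out. It is simply not specified.
- The exact factor of two needs 500 patients in total, split evenly and treated as independent. If 500 meant pairs, 0.125 would be the detectable within-pair difference in SDs of that difference, although *across time* would not describe it.
- Aim 1 already states case-control sensitivity for UPOU as detectable odds ratios of 1.38 to 1.55 at 600/600.
- Nothing in the plan uses 0.13 as a decision criterion; models are trimmed by information criteria and RMSEA.

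These points stand, and they rule out calling 0.13 a proven error of that size. They do not rescue the sentence. If a correlation was meant, SD units *across time* is the wrong label. If a change was meant, the SEM section has no outcome to match it.

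It is also tempting to quote a clinician-level detectable difference of about 0.46 SD, from 2.802·√(2/74). That assumes 148 clinicians split 74/74. The documents give no such split, and a clinician who prescribed to several patients is not inherently a case or a control unit. It can serve only as an illustration under an assumed even split, before clustering.

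**Conclusion.** The point holds as a mismatch between the power statement and the analysis it supports. The quoted 0.13 SD fits a one-group change or a correlation, while the specified outcome is case versus control. On the mean-difference scale the detectable effect is about 0.25 SD at 250/250 (0.21 SD as pairs with r = 0.3), 0.16 SD at the planned 600/600 and 0.175 SD at the recruited 513/517.

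Except for the paired value, these figures assume independent groups. All are for a single observed patient-level predictor, with no clustering by clinician or site and no measurement error in latent variables.

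It does not follow that Aim 3 is underpowered at patient level. A difference of 0.16 or 0.175 SD is still small, so the article's conclusion largely survives there. What is unsupported is the figure itself and any extension of it to clinician-level or practice-level predictors.

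**What to change.** In Specific Aim 3, Sample Size Estimates:

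1. Name the effect measure and the test behind the detectable effect.
2. Delete *across time*, or tie it to a longitudinal outcome defined in the SEM section.
3. Replace 0.13 SD at n = 500 with the case-control figures at the planned 1200 (0.16 SD) and the achieved 1030 (0.175 SD). Mark them as applying to a single observed patient-level predictor, with independent groups and no clustering or latent-variable measurement error.
4. State that these figures do not carry over to clinician-level or practice-level predictors, and give the 148 responding clinicians against the 410 to 760 anticipated. Do not print 0.46 SD as a result.

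This changes wording only: no data collection and no change to the analysis. The stated sensitivity becomes somewhat less favourable. The article reports the SEMs as still under development, so the correction can be made before their results are interpreted.

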#### National Administrative Claims Database Analysis

The data collected prospectively on clinicians and patients at the 3 clinical sites provided detailed data on patients and clinicians from varied settings but were necessarily limited in sample size and derived from institutions affiliated with academic medical centers. As a result, a large national claims database was used to explore the findings of this study in a much larger and more diverse population.

The OLDW is an open, collaborative research and innovation center founded in 2013 [65]. The core linked data assets include deidentified claims data for privately insured and Medicare Advantage enrollees and deidentified EHR data from a nationwide network of provider groups. The database contains longitudinal health information on enrollees and patients, representing a diverse mixture of ages, ethnicities, and geographical regions across the United States. The EHR data are sourced from provider groups and reflects all payers, including uninsured patients.

The OLDW was used to estimate a structural model similar to that used in the analyses of clinical data from aims 1 and 2. The latent factors representing clinician, patient, and environmental factors associated with patients developing OPOU were estimated using OLDW data, and the results were compared with those estimated in the clinical data. The OLDW contains beneficiary characteristics including gender, age, race and ethnicity, household income, and geography (ie, state, county, or zip code). For beneficiaries submitting health insurance claims, a broad range of information is available including pharmacy claims (ie, prescribing clinician, drug type and date dispensed, days of supply), clinician and facility claims (ie, Current Procedural Terminology 4 codes, *International Classification of Diseases* [*ICD*]-*9* or *ICD-10* procedure codes, and *ICD-9* or *ICD-10* diagnoses), dates and place of service, cost data (ie, charges and patient and insurance amounts paid), and clinician type and specialty. In addition, OLDW includes laboratory data for 30% to 40% of patients whose clinicians have contracted with laboratories that provide data to OLDW.

Many of the concepts to be tested with clinical data were approximated using administrative claims data. Diagnostic codes were used to measure comorbidities including depression, anxiety and substance use disorders. Procedure and diagnostic codes were used to infer pain etiology from surgery, trauma, and other causes. Place of service and clinician specialty codes were used along with prescription fill information to determine the source of opioid prescriptions. Patient geographic information and prescription fill information were used to determine regulations governing the use of prescription drug monitoring programs.

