### Study Objectives

In this research project, 3 Clinical and Translational Science Awards (CTSA) programs (Mayo Clinic, University of Michigan, and Yale University) leveraged the conceptual framework for UPOU to investigate how the patient characteristics, practice environment characteristics, and opioid prescriber characteristics facilitate or impede UPOU. All data management and analyses were conducted at a fourth CTSA program (University of Minnesota). This work was accomplished by pursuing three specific aims.

#### Specific Aim 1

The first aim was to identify incident cases of UPOU and prospectively assess their characteristics in comparison to new opioid users who did not progress to UPOU. At each site, opioid-naive adults receiving opioid prescriptions were enrolled. Opioid prescriptions and self-reported opioid use were followed, and patients progressing to UPOU were identified in real time. A matched sample of patients who did not develop UPOU were recruited for assessment of framework elements, including biochemical confirmation of opioid use, pain-related measures of physical and emotional functioning, and medical and social histories.

#### Specific Aim 2

The second aim was to assess clinicians prescribing opioids to incident cases of UPOU and new opioid users who did not progress to UPOU. Clinicians treating patients recruited in aim 1 were recruited for prospective assessment of prescriber characteristics including questions about past training in pain management, and attitudes and beliefs about pain and opioid use. The practice environment was assessed including practice organization, practice size, and estimated proportion of patients receiving pain management services.

#### Specific Aim 3

The third aim was to evaluate the conceptual framework. Using the information gathered in aims 1 and 2, structural equation modeling (SEM) was used to evaluate the associations between framework elements in each domain. Identified interactions were further evaluated in a large nationally representative administrative claims database.

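### The claims-database comparison changes the measures as well as the population, and the article's own example interaction has no listed OLDW variable

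*Protocol article*

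**What the plan says.** All references are to the protocol article.

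- **Purpose.** National Administrative Claims Database Analysis gives an exploratory aim: "a large national claims database was used to explore the findings of this study in a much larger and more diverse population".
- **Model and comparison.** The same section says "The OLDW was used to estimate a structural model similar to that used in the analyses of clinical data from aims 1 and 2", and that clinician, patient and environmental latent factors "were estimated using OLDW data, and the results were compared with those estimated in the clinical data".
- **Measurement.** It discloses that "Many of the concepts to be tested with clinical data were approximated using administrative claims data". Among the proxies, "Diagnostic codes were used to measure comorbidities including depression, anxiety and substance use disorders".
- **Interactions.** Study Objectives, Specific Aim 3, states: "Identified interactions were further evaluated in a large nationally representative administrative claims database". The Methods overview repeats this.
- **Clinical side.** SEM Analysis gives, as examples of unobserved patient constructs, "symptoms of opioid withdrawal, opioid craving, and the psychosocial impact of chronic pain". Its example of a cross-level interaction is: "For example, the effects of pain management training on UPOU varied by patient age".

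**The concern.** The OLDW step is there to show whether relations found at three academic centers appear in a wider population. That inference needs the same quantities, adjusted for the same things, in both sources. Here the population and the measures change together. A path that shrinks or vanishes in OLDW may mean that the finding does not generalize, or only that a code replaced a symptom scale. A path that persists may do so partly because it has taken up the effect of a correlated construct that OLDW lacks.

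The result will be used. Principal Findings expects OLDW to help wide dissemination, and the Discussion treats the step as secondary testing that will help in designing later research. Limitations does not mention the mismatch. Yet Principal Findings itself partly blames claims data for the imprecision of an earlier meta-analysis, and justifies the symptom scales by the imprecision of past psychiatric diagnoses.

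**Working it through.** The article states no figure for this comparison, so there is none to reproduce. The check is a map of variables, followed by two illustrations on assumed inputs.

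**1. Clinical constructs against listed OLDW variables**

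| Clinical construct (Aim 1 and Aim 2 assessments) | Counterpart named for OLDW |
|---|---|
| Age, sex, ethnicity | Age, gender, race and ethnicity |
| Surgical or nonsurgical indication | Procedure and diagnosis codes |
| Clinician's professional training category (CAOS) | Clinician type and specialty |
| Prescriptions | Pharmacy claims (dispensed) |
| Depressive symptoms (CES-D) | Diagnosis codes |
| Misuse and substance use instruments | Substance use disorder codes |
| Craving, withdrawal | None named |
| Pain intensity, body map, MPI | None named |
| Catastrophizing | None named |
| Heat pain testing | None named |
| Clinician attitudes, beliefs, pain training | None named |

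All three unobserved patient constructs that SEM Analysis gives as examples fall in the rows with no named counterpart.

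**2. The example interaction**

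Training by patient age needs both variables. Age is listed for OLDW. Pain management training is not; the listed clinician attributes are prescriber identity, type and specialty. On those variables, the statement in Study Objectives cannot be met for this example.

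**3. Replacing a scale by a code (assumed inputs)**

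Let p be the true prevalence, Se the sensitivity and Sp the specificity of the code. Observed prevalence is q = Se·p + (1 − Sp)(1 − p).

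Assume control prevalence p0 = 0.30, a true OR of 1.55 and Sp = 0.95. Then p1 = 1.55 × 0.30 / (0.70 + 1.55 × 0.30) = 0.465/1.165 = 0.399.

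| Se | q in cases | q in controls | Observed OR |
|---|---|---|---|
| 0.4 | 0.190 | 0.155 | 1.28 |
| 0.5 | 0.230 | 0.185 | 1.31 |
| 0.7 | 0.309 | 0.245 | 1.38 |

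For other inputs, take the article's detectable OR of 1.38 at control prevalence 0.5. With Se from 0.3 to 0.9 and Sp from 0.90 to 0.98 (both assumed), the observed OR runs from 1.10 to 1.33. The true OR is held equal in both sources throughout, so all of the attenuation comes from measurement.

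**4. Leaving out a correlated construct (assumed inputs)**

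In a linear approximation with standardized variables, dropping a construct that has path b and correlation r with the retained one changes the retained path by r·b. Take a retained path of 0.13, the effect size in the Aim 3 Sample Size Estimates, and assume b = 0.3:

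- r = −0.3: 0.13 − 0.09 = 0.04
- r = 0.5: 0.13 + 0.15 = 0.28

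Omission can therefore push the path either way, and can mask agreement as well as create it.

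**5. Other differences between the sources**

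Limitations says that clinical case status rests on prescriptions issued, whereas OLDW pharmacy claims record dispensing. The clinical sample is a 1:1 time-matched case-control sample taken at day 90, whereas OLDW is a database of enrollees and patients.

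**The case against.** A reader might infer that OLDW lacks most of the clinical model's constructs, that it is set against the full clinical model, and that the step can show nothing about generalization. The article does not support any of these readings.

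- The map covers the constructs collected, not those in the final model. SEM Analysis trims each domain to a parsimonious set, and Results says that the SEMs are still being developed. Which constructs survive is unknown.
- The text says a similar model, and does not say that the full clinical model is the comparator. The exact comparison may be set out in a fuller plan that is not shown, so the absence of concordance criteria is not counted here.
- OLDW also holds EHR data from provider groups, and laboratory data for 30% to 40% of patients. The EHR fields are not described, so a measure such as pain intensity cannot be ruled out.
- The approximation is disclosed and the purpose is called exploratory. Age, sex, etiology and specialty remain informative, though with different adjustment.
- Dissemination is said to be helped by OLDW, not to depend on it. Training by age is given only as an example.
- The misclassification figures are assumed, and they describe a single marginal odds ratio rather than a latent path.

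All of this stands and limits the claim. It does not meet the remaining point. The article commits to a comparison and, without qualification, to evaluating the interactions, on a variable list that has no measure for several candidate constructs or for its own example.

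**Conclusion.** The concern holds in a limited form. On the variables listed, the comparison mixes a change of population with a change of measurement and adjustment, so neither agreement nor disagreement can be attributed to the population. Evaluation of identified interactions cannot be delivered for the article's own example. The size of the distortion is unknown. The odds ratios of 1.28 to 1.38 against a true 1.55 show only that code-based measurement could produce an apparent difference; prevalence, sensitivity and specificity are assumptions. The conclusion also assumes that the named proxies reflect what will be used and that at least some unmatched constructs survive trimming. This is an inexpensive improvement to an analysis not yet run; it does not invalidate Aims 1 and 2.

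**What to change.** 1. Add a bridging analysis: refit the clinical SEM in the 1030 patients with only those constructs that also exist in OLDW (demographics, surgical or nonsurgical etiology, comorbidity history, prescriber specialty, prescriptions), coded as closely as the data in hand allow.
2. Compare OLDW with this reduced model. Report the full against the reduced clinical model to show how much the change of variables matters.
3. Do not present reduced-clinical against OLDW as a pure population effect, because case-control sampling and issued versus dispensed prescriptions still differ.
4. Restrict the Aim 3 statements in Study Objectives and the Methods overview, and the secondary-testing claim in the Discussion, to constructs and interactions measurable in OLDW. List those that are not.

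**Cost.** One more model fit, some recoding, and a narrower Aim 3 claim. The medical and psychiatric histories already collected may be enough for the comorbidity variables. If coded diagnoses are wanted, they must be extracted: the EHR review described is for opioid prescriptions, and the data were deidentified before analysis, so linkage needs checking. If prescriber specialty can be taken from the prescribing record, the reduced model need not depend on the 148 clinicians who completed the survey, none of them at Yale.
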